### Data management

#### Data collection

Research assistants (at least two at each site) dedicated for data collection and regional coordinators (one for each region) will be trained on data collection and quality control procedures, including correction of errors and safe transfer of data to the central research server. The clinical data (process and patient outcomes) collected at each facility will be entered into an electronic data collection system i.e. Open Data Kit (ODK) developed specifically for this project. Refresher training of research assistants will be conducted by the study investigators and data manager as needed. Data will prospectively be collected at all sites for a period of 3 years. Clinical process and patient data will not include personal information: instead a unique identification (ID) number will be provided. The regional coordinators will oversee the data collection processes at the regional level. Several datasets will be collected during both baseline and implementation phases. We will monitor implementation level data (e.g. facilitators and barriers for scale-up), process level data (e.g. the adoption of training, use and experiences with the SBBC tools), and outcome/output level data (patient outcomes, clinical actions, and biomedical signal data).

##### Implementation level data

A facility readiness and service availability assessment tool will be used to conduct bottleneck analyses of each health facility readiness for good quality intrapartum care. A quality improvement tool will be used to develop a specific plan based on the bottleneck analysis. Knowledge about CQI process implementation at SBBC sites will be collected using Logbooks and PDSA diaries.

##### Process level data

Systems will be established to document the dissemination of trainings and the frequency and quality (performance) of training among healthcare workers in each site over the 3 years. On-site simulation training data will be semi-automatically collected by the NeoNatalie Live simulator and uploaded automatically to the central server at Haydom. Healthcare workers’ knowledge and skills on intrapartum care before and after the initial 5-day training will be collected using multiple-choice questions and OSCEs. Their periodic skills retention tests will be done using OSCEs.

The adoption of the SBBC will be further evaluated through in-depth interviews and focus group discussions with healthcare workers, caregivers, and facility leaders/management. Healthcare workers will be asked to ascertain acceptability and barriers of the new interventions. The perceptions of women about intrapartum care will be assessed with semi-structured interviews.

##### Outcome/output level data

Patient morbidity, mortality and clinical events/actions during intrapartum care data will be collected from patient case notes, labour and delivery registers. The use of clinical SBBC tools (Moyo, NeoBeat and Upright bag mask) will be recorded on separate data collection forms Biomedical heart rate signal data will be automatically collected by Moyo (foetal heart rate) and NeoBeat (newborn heart rate).

#### Data transfer and quality control

In each facility, the research assistants will assess the quality and completeness of the data before uploading via the electronic data collection system into the central secure research server/database at Haydom Lutheran Hospital. Signal data collected by Moyo and NeoBeat will automatically upload to the research server. The regional coordinators will perform quality data check on a daily basis. A data manager, located centrally at Haydom, will be responsible for overseeing the data management process including quality control. The data manager will run queries and perform final quality control before saving the data on the secure research server. Any querry identified will be sent back to the regional coordinator who will communicate with the research assistants for resolution. Training data will be collected partly automatically by the NeoNatalie Live simulator and others will be manually entered into the database immediately after training. De-identified qualitative data will be collected using digital recorders. They will be transcript, processed and stored in password protected research computers with controlled access.

#### Feedback of data

After data correction and cleaning, the data manager will prepare summary tables of selected variables identified for rapid evaluation of study progress. The summary tables will be shared with the regional coordinators, health management team in the regions and health facilities, and the national and site facilitators. The feedback will then be shared with healthcare workers and utilized to assess the strengths and identify procedure-practice gaps which need improvement, in line with the PDSA model and CQI. Some facilities will have direct access to their own “dashboard” (Fig. 3) and can follow their daily statistics.

### Data analysis

A final data analysis plan will be established in collaboration with the respective ministries, principal investigators and statistical partners in the consortium to answer all the specific project objectives. For binary correlated data (e.g. before and after training practices for health care workers), the one-sided McNemar’s test will be considered. Differences in training attendance and knowledge and skills acquisition rates between health-facilities will be compared using both bivariate and logistic regressions. The training scores will be modelled as longitudinal data and compared over time using time series analyses and mixed model effects. Statistical process control methods will also be utilised. The clinical care indicators and perinatal/maternal outcomes will be analysed and compared both within and between clusters/facilities (and regions) by random intercept models factoring in the stepped-wedge design. Poisson regression models will be used to estimate the differences in rates of morbidity and mortality. Qualitative thematic content data analysis methods will be used to analyse qualitative data [52]. Qualitative data will be processed and analysed using COREQ guidelines [53].

## Discussion

Successful implementation of SBBC in Tanzania has the potential to improve quality of care and save thousands of lives during labour and after birth. Better trained and equipped healthcare workers in health facilities with access to LDHF training, and data-driven feedback stand a better chance to save more perinatal and maternal lives.

The SBBC will provide healthcare workers with Moyo FHR monitors to facilitate labour management, i.e. timely identification of foetuses who needs urgent obstetric interventions. The use of NeoBeat for quick assessment of non-breathing neonates immediately after birth will help distinguishing true FSB from severely asphyxiated neonates, reducing misclassification of FSB and facilitate timely decisions to start resuscitation. The use of training equipment (MamaNatalie and NeoNatalie) including CQI PDSA cycles, will ensure skills promotion, retention and build competence and confidence among the healthcare workers.

Previous Safer Births studies [23, 28, 35, 43, 44, 54–58] testing the individual innovations and/or interventions on a smaller scale, have reported improvements in quality of care and saving lives. Generating evidence-based knowledge on quality of care around birth from large scale interventions is a key priority to reach the SDG targets 3.1 and 3.2 of reducing preventable maternal and perinatal mortalities [59, 60]. Facilities need to provide a safe and professional environment, enabling well-educated and skilled healthcare workers to perform optimally with essential resources available (SDGs 3c/4.7) [61, 62]. This is simultaneously pivotal for assuring respectful working conditions for healthcare workers (SDG 8.8).

The Safer Births innovations (www.saferbirths.com) have been developed, tested separately, and proven effective in changing clinical behaviour and improving birth outcomes to cater for these global SDG targets. We will now study the impact of the combined SBBC package on improving quality of intrapartum care and perinatal outcomes at scale. In addition, the project will provide contextual information on requirements to scale up implementation of these innovative interventions to health-facilities in low resource settings.

There are several strengths of our study. Firstly, we will integrate the new clinical and training SBBC tools with existing national guidelines and initiatives to ensure sustainability of the interventions. Secondly, we will use the proven LDHF on-the-job training concept, utilizing birth and newborn simulators, to ensure skills acquisition, translation, and retention. Thirdly, the study will involve rapid local data-driven feedback to stimulate CQI efforts, improving quality of care and patient outcomes at the local facility.

The project has several limitations especially related to the stepped-wedged design. Firstly, this design includes a potential contamination risk of the baseline/control periods of later wedges/clusters, which may dilute the effects. Secondly, unlike the traditional cluster randomised trials, the stepped-wedge design may pose a challenge of adherence to the randomisation sequence as some regions may feel they are being delayed in implementing the interventions. Thirdly, if national policy changes occur, they may affect some of the wedges/clusters and accommodating these changes during the trial period pose a challenge [63]. Fourthly, in the SBBC project, a number of clusters (hospitals) will be allocated to a number of wedges (regions). Each wedge will contain a relatively small number of clusters (*n* = 6) receiving the intervention at different times. The final large number of clusters (*n* = 30) and the various crossovers taking place at different times, make it difficult to adapt the CONSORT diagram, often used when reporting classical cluster randomised controlled studies [64]. Another feature posing challenges in reporting results, is the assessment of whether the randomisation has resulted in balanced study conditions at baseline given the small number of clusters in each wedge. For this reason, a baseline table will be used to present baseline characteristics of all clusters [64, 65].

Our findings will be published as multiple papers in peer-reviewed relevant Open-Access international journals and communicated on global conferences. Summary reports, in popular language, will be developed for policymakers; outlining required quality improvement frameworks for improving care to advocate for more investments in such interventions. Combined workshops and dissemination seminars with relevant stakeholders will be conducted locally. The aim will be to summarize and discuss the findings from the ongoing data collection and related implications for operational changes in care at birth, as well as in development and implementation of PDSA cycles as part of CQI.

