## Methods

### Study design

This is a continuous quality improvement (CQI) project, which will be implemented in a stratified stepped-wedge cluster (regions) randomisation approach (Fig. 1). Randomization was done using simple random sampling i.e. the first region, Manyara, was purposively selected for logistical and strategic reasons, whereas subsequent regions were selected randomly. Clusters will receive the intervention at different time points based on the randomization [45]. Prospective observational data will be collected before and after introduction of the intervention periods at each cluster. The before implementation data, collected for three to 12 months (Fig. 1), will serve as baseline/control data. Random and sequential crossover of clusters from control to intervention will be conducted until all clusters are exposed. More clusters will be exposed to the intervention towards the end of the study.

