#### Q stands for quarter of the respective year

This design is preferred because, firstly, it provides a robust scientific evaluation of health service delivery of interventions, and it does not involve individual patient recruitment, rather a cluster (i.e. health facilities in one region). Secondly, for ethical purposes it ensures that all clusters receive the proven beneficial interventions by the end of the project. Thirdly, not all health facilities will implement the bundle at the same time, but in a stepwise manner, providing a learning opportunity for more optimal implementation at the next facilities. Data collected at each facility and context-specific issues will inform local training models and use of effective plan-do-study-act (P-D-S-A) cycles as study implementation continues [46, 47].

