### Sites

The project will be implemented in 30 health facilities in 5 clusters (regions) in mainland Tanzania: Manyara, Tabora, Geita, Shinyanga, and Mwanza as described in Fig. 1. These health facilities were selected in consultation with the Tanzania Ministry of Health Community Development, Gender, Elderly and Children (MoHCDGEC) and the President’s Office- Regional Administration and Local Government (PO-RALG) based on the following criteria: 1) high burden of maternal and perinatal mortality, 2) high volume of deliveries, and 3) alignment with the ministry’s strategic priorities for maternal and newborn interventions in the country. Table 1 shows total births, fresh stillbirth rates, macerated stillbirth rates, 7-days neonatal mortality and maternal mortality rates in 2019 for the 30 health facilities. The data was obtained from respective health facility records of the health management information system. All of the health facilities provide Comprehensive Emergency Obstetric and Basic Newborn Care services and have separate labour units and operating theatres.

**Table 1 Tab1:** Total birth and mortality rate in the study hospitals (2019)

Region	Health Facility	Births	Fresh Stillbirth rate (per 1000 live births)	Macerated Stillbirth rate (per 1000 births)	7-day neonatal mortality rate (per 1000 live births	Maternal mortality per 100,000 births
Manyara	Dareda	3333	2.4	14.1	6.0	NA
	Babati DH	3342	1.5	5.7	3.0	149.6
	Tumaini DH	2964	6.1	6.1	4.0	NA
	Kibaya DH	1808	21.6	16.6	13.3	165.9
	Mbulu DH	3275	6.4	6.4	NA	NA
	Mererani HC	1123	0.9	5.3	NA	NA
Tabora	Igunga DH	5378	11.2	11.5	10.6	185.9
	Nzega DH	4441	7.4	18.7	NA	NA
	Kitunda HC	1331	6.0	6.0	Na	NA
	Kitete RRH	5202	18.5	22.9	4.6	NA
	Urambo DH	2812	26.3	19.2	1.4	106.7
	Upuge HC	579	15.5	NA	NA	NA
Geita	Uyovu HC	3945	0.5	1.8	1.0	50.7
	Chato DH	3430	2.3	1.5	2.3	145.8
	Katoro HC	7154	3.5	3.2	0.3	83.9
	Nzera DH	3974	1.5	1.5	NA	75.5
	Geita RRH	7199	18.9	16.8	13.3	291.7
	Masumbwe HC	3296	2.1	3.6	NA	364.1
Shinyanga	Kahama DH	9559	14.8	17.9	10.5	73.2
	Bugarama HC	1757	1.1	0.6	NA	NA
	NINDO HC	1993	8.5	5.0	4.5	351.2
	Kambarage HC	2512	4.8	3.2	NA	NA
	Shinyanga RRH	4206	30.9	20.4	25.9	428.0
	Bulungwa	1951	0.5	NA	NA	NA
Mwanza	Buzuruga HC	2579	0.8	5.8	1.6	NA
	Sekou Toure RRH	9024	15.1	19.8	6.6	110.8
	Magu DH	3304	13.3	21.5	NA	NA
	Nyamagana DH	7619	7.9	11.8	1.4	78.8
	Sengerema DDH	10,064	10.2	12.2	19.7	218.6
	Nansio DH	4339	11.5	7.1	NA	NA

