### Study population and sample size estimation

The study will include parturient women, their offspring, and healthcare workers in the 30 selected health facilities. Pregnant women at gestational age 28 weeks and above with a live foetus at labour admission will be enrolled in the study. All healthcare workers in the maternity ward (prenatal, labour, postnatal and neonatal wards) in the selected health facilities will be involved.

We used Stata function stepped-wedge to calculate the power [50] with the following input parameters. An average of 4000 baby-mother pairs per year per health facility giving an estimate of 240,000 baby-mother pairs for a 2-years duration (i.e., an average of 1 year pre-implementation and 1 year post implementation), 25% reduction in perinatal mortality from 2 to 1.5% at a two-sided significance level of 5%. Assuming intracluster correlation coefficient (ICC) to be 0.0013 [51], the study power stands at 0.99.

Purposive sampling will be used in the qualitative components of the study. Maximum variation sampling will guide the selection of participants for in-depth interviews and focus group discussion with healthcare workers, facility management team as well as mothers receiving care. This approach secures a wide variety of people of interest and consequently a broad range of perspectives to better understand contextual factors influencing implementation. Qualitative data will be collected until saturation is achieved.

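### The randomised unit is the region (five, four in random order), yet the protocol also calls the 30 hospitals the clusters and leaves the level of its ICC unstated; the planned random-intercept models would understate standard errors if regional rates shift over time

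*Protocol article*

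**What the plan says.** Three places in the Methods make the region the cluster. Study design describes a project "implemented in a stratified stepped-wedge cluster (regions) randomisation approach" and adds that "the first region, Manyara, was purposively selected for logistical and strategic reasons, whereas subsequent regions were selected randomly". The design rationale below Fig. 1 says that the unit recruited is not the patient, "rather a cluster (i.e. health facilities in one region". Sites states: "The project will be implemented in 30 health facilities in 5 clusters (regions) in mainland Tanzania".

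The limitations in the Discussion use the word differently: "a number of clusters (hospitals) will be allocated to a number of wedges (regions". Each wedge then holds six clusters and the total is 30, which the text calls large.

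The sample-size section uses a Stata stepped-wedge routine for a fall from 2% to 1.5%, with 240,000 pairs and a two-sided 5% level: "Assuming intracluster correlation coefficient (ICC) to be 0.0013", power is 0.99. The number of clusters, the steps and the level of the ICC are not given.

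Data analysis says that clinical indicators and perinatal and maternal outcomes will be "analysed and compared both within and between clusters/facilities (and regions) by random intercept models factoring in the stepped-wedge design". It also says that a final analysis plan is still to be established.

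**The concern.** In a stepped-wedge trial the evidence comes from the units that change over independently. Here those are regions, and one of the five was placed first on purpose. Describing the design as having a large number of clusters suggests more randomised information than there is.

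The label matters because it carries into the model and the power figure. A random intercept for a facility or a region removes a constant difference in level. It does not remove a rise or fall that all six facilities of a region share in some months. Such a shift can coincide with that region's crossover and be read as a treatment effect.

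The protocol gives reasons to expect shared shifts. Its limitations mention national policy changes that may reach only some wedges. Each region has its own coordinator and its own training batch, and regional management teams receive the data feedback. At stake are the confidence interval and p-value for the primary outcome, perinatal mortality.

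**Working it through.** **1. The plan's own figure.** Inputs from the sample-size section: 2% to 1.5% (difference δ = 0.005, mean rate 0.0175), ICC 0.0013, and 240,000 / 30 = 8000 pairs per facility. Assumed, because Fig. 1 is not shown: six equal periods with one region crossing at each step. The model has fixed period effects and a random cluster intercept. Power = Φ(δ/SE − 1.96).

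- 30 facilities as clusters: SE = 0.000931; 0.005/0.000931 = 5.37; Φ(3.41) = 0.9997. With 1000 pairs per facility-period: SE = 0.001066, power 0.997.
- 5 regions as clusters: SE = 0.000954; 5.24; Φ(3.28) = 0.9995.

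The 0.99 is reproduced with either unit. Changing the unit alone does not lower power under this model with a normal reference.

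**2. Adding region-by-quarter variation.** Assumed layout: 24 months; crossover at months 3, 5, 8, 10 and 12, with regions in the order listed under Sites; Table 1 births spread evenly over the year; fixed month effects. Variance components at a mean rate of 1.75%:

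- individual: σ² = 0.0175 × 0.9825 = 0.01719
- facility intercept: τ² = 0.0013 × 0.01719 = 0.0000224
- region-by-quarter SD: ω = 5%, 10% or 15% of 0.0175, that is 0.000875, 0.00175 or 0.002625. The documents give no value for ω.

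If the analysis uses facility intercepts only, its model SE is 1.101 per 1000 whatever ω is. The true SE of that estimator follows from its sandwich variance, and true error = 2Φ(−1.96 × model SE / true SE).

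| ω, % of rate | True SE per 1000 | Ratio | True error of nominal 5% test |
|---|---|---|---|
| 0 | 1.101 | 1.00 | 5.0% |
| 5 | 1.214 | 1.10 | 7.5% |
| 10 | 1.503 | 1.37 | 15% |
| 15 | 1.888 | 1.72 | 25% |

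At a flat rate of 2% the last three errors are 7.9%, 16% and 28%. In the six-period layout of step 1, with region-by-period variance at 5% to 50% of the ICC variance, the error runs from 0.11 to 0.42. The direction does not depend on the layout.

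**3. Power when that variation is modelled** (δ = 0.005; noncentral t for the t columns).

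| ω, % of rate | SE per 1000 | Normal | t, 27 df | t, 3 df |
|---|---|---|---|---|
| 0 | 1.101 | 0.995 | 0.99 | 0.84 |
| 5 | 1.205 | 0.99 | 0.98 | 0.78 |
| 10 | 1.416 | 0.94 | 0.93 | 0.66 |
| 15 | 1.618 | 0.87 | 0.85 | 0.56 |

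The 27 df are 5 × 8 = 40 region-quarters less 5 region, 7 quarter and 1 treatment terms. The 3 df are five regions less two, a conservative convention.

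**4. Does the ICC level matter?** An ANOVA ICC for fresh stillbirth in Table 1 is 0.0056 between the 30 facilities and 0.0013 between the five regions. These are one-year level differences in one component of the primary outcome. They show that the level needs stating, not which level the protocol used.

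**5. Permutation limit.** With Manyara fixed first there are 4! = 24 orders, so the smallest possible p-value is 1/24 = 0.042.

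**The case against.** The strongest reply is that this is a condensed article with a final analysis plan still to come. Random-effect structure and small-sample corrections are commonly settled there, and the Data analysis section does mention regions. That stands as far as omissions go: the article cannot be said to have decided against a region-by-time term. But it does name a model class, and intercepts at either level or both do not do this job. The conflicting cluster definitions and the unlabelled ICC are also on the page, whatever the later plan says.

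Four stronger readings are tempting, and the documents do not support them.

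- **The standard errors are too small.** This holds only if region-by-period variance is above zero. The documents give no figure for it, Table 1 covers a single year, and with zero variance the model SE is correct.
- **The 0.99 is wrong.** It is reproduced from the stated inputs with 30 facilities or with five regions.
- **True power is nearer 0.56.** The low figures come mostly from choosing 3 df. If region-by-quarter effects are independent, 27 df fits the model, and power stays at 0.85 or above across the range shown. The 3 df convention is a caution, for instance if regional effects persist across quarters.
- **The permutation limit is a defect.** It is below 0.05, and no permutation test is planned.

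The layout is also assumed. The protocol plans three years of data collection, and the crossover months are only choices within its three to 12 months of baseline.

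**Conclusion.** Two things are established from the text alone. The cluster is the region in the Methods and the hospital in the Discussion, and the ICC behind the 0.99 has no stated level, cluster number or steps. Only the region is compatible with how the intervention is allocated.

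The consequence for inference is conditional. If regional rates shift over time, as the protocol's own limitations allow, a random-intercept analysis will be too optimistic: mildly at an SD of 5% of the rate, seriously at 10% to 15%. The 0.99 is a property of a model with no such variation and a large-sample reference. With a normal reference it barely moves at 5% (0.986) and falls to 0.87 at 15%. These sizes rest on the assumed crossover months, 24 months of data, Table 1 births, a 1.75% mean rate and the assumed SDs. They illustrate the problem and do not estimate what this trial will show.

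**What to change.** - State throughout that the region is the randomised unit, with five regions, four of them in random order, and that the 30 facilities are nested within regions. Correct the limitations paragraph to match.
- Add a region-by-period random effect (for example region-by-quarter) to the facility intercepts and calendar-time effects in the primary model.
- Specify a small-sample correction suited to five regions. Add a permutation test over the 24 orders as a sensitivity analysis only, noting its minimum p-value of 0.042.
- State the ICC level, the number of clusters and the steps behind the 0.99, and report power over a range of between-period correlations below 1.

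The cost is revised wording, one more variance component and a recomputed power figure; no new data are needed. The final analysis plan is still to be written, so the change fits there. The downside is wider intervals and a less favourable stated power.
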